**Demographics**	
Gestational age at birth	Number of weeks from the first day of the women's last menstrual cycle until birth. Round up or down to the nearest week.
Age at presentation (in hours)	We understand this information may be difficult to obtain - please be as accurate as you can. Please round to the nearest hour. This number may be very large for patients who have a delayed presentation - please still enter it. For neonates born within your centre please enter 0. Enter unknown if unknown.
Gender	Male, Female, Ambiguous, Unknown.
Weight at presentation	In kilograms (kg) on the day of presentation. Please provide a value to one decimal place.
Does the patient have another anomaly in addition to the study condition?	Yes: Cardiovascular, Yes: Respiratory, Yes: Gastrointestinal, Yes: Neurological, Yes: Genito-urinary, Yes: Musculoskeletal, Yes: Down syndrome, Yes: Beckwith-Wiedemann syndrome, Yes: Cystic fibrosis, Yes: Chromosomal, Yes: Other, No. Select all that apply. Include all anomalies diagnosed at any stage up until 30 days post-primary intervention or 30 days following presentation for those who did not receive an intervention. If you suspect an associated anomaly, but it has yet to be diagnosed, select 'Yes: Other'.
Distance from the patient's home to your hospital	In kilometres (km). Please round to the nearest kilometre. Please enter 0 if born in your hospital.
**Antenatal care and delivery**	
Antenatal ultrasound undertaken? If the condition was diagnosed antenatally, at what gestational age?	Yes: study condition diagnosed, Yes: problem identified but study condition not diagnosed, Yes: no problem identified, No. Please round up to the nearest week. If the patient has more than one study condition, please note the gestational age at which one or more of the conditions was first diagnosed.
Mode of transport to hospital? Where did the patient present from? If other, please specify.	Ambulance, Other transport provided by the health service, Patient's own transport, Born within the hospital. Home, Community Clinic, General Practice, District Hospital, Other, Unknown. District hospital includes secondary-level healthcare, provincial hospital, general hospital, general mission hospital or regional hospital. It has general anaesthesia and can provide general surgical care.
Type of delivery:	Vaginal (spontaneous), Vaginal (induced), Caesarean section (elective), Caesarean section (urgent/non-elective), Unknown. Vaginal delivery includes those requiring forceps and ventouse.
**Clinical condition and patient care**	
Was the patient septic on arrival? If yes, were appropriate antibiotics administered?	Yes, no. Sepsis is SIRS with a suspected or confirmed bacterial, viral or fungal cause. SIRS is a response to a stimulus, which results in two or more of the following: temperature >38.5°C or <36°C, tachycardia*, bradycardia* in children <1 year old, tachypnoea*, leucopenia or leucocytosis*, hyperglycaemia*, altered mental status, hyperlactaemia*, increased central capillary refill time >2 seconds. Arrival is the time of birth for neonates born at your hospital. *Variables are defined as values outside the normal range for age. Yes: within 1 hour of arrival, Yes: within the first day of arrival, No. Appropriate antibiotics are defined as either broad spectrum covering gram negative, gram positive and anaerobic bacteria OR antibiotics that are the standard empirical treatment for that condition according to local guidelines OR are based on sensitivities provided by a microbiology sample.
Was the patient hypovolaemic on arrival? If yes, was an intravenous fluid bolus given? If yes, how much intravenous fluid was given?	Yes, No. Criteria for diagnosis include at least one of the following: prolonged central capillary refill time >2 seconds, *tachycardia, mottled skin, *reduced urine output, cyanosis, impaired consciousness, *hypotension. *Variables are defined as values outside the normal range for age. Yes: within 1 hour of arrival, Yes: on the first day of arrival, No. 10–20 mL/kg, >20 mL/kg. If <10 mL/kg was given, please select 'no' for the question asking if intravenous fluid was given.
Was the patient hypothermic on arrival? If yes, was the patient warmed on arrival to within a normal temperature range?	Yes, No. Defined as <36.5°C core temperature. Arrival is the time of birth for neonates born at your hospital. Yes, No. Only select yes if warming was commenced within 1 hour of arrival. Arrival is the time of birth for neonates born at your hospital.
Did the patient receive central venous access? If yes, did the patient acquire central line sepsis?	Yes: umbilical catheter, Yes: peripherally inserted central catheter, Yes: percutaneously inserted central line with ultrasound guidance, Yes: surgically placed central line (open insertion), No. Please select all that the patient received within 30 days of primary intervention or 30 days of presentation if no intervention was undertaken. Yes: diagnosed clinically, Yes: confirmed on microbiology, No. Within 30 days of primary intervention or 30 days of presentation if no intervention was undertaken.
Time from arrival at your hospital to primary intervention in hours	Enter 0 if no intervention was undertaken. *Primary intervention for each condition is defined as follows.* *Oesophageal atresia*: surgery, either temporising or definitive, to manage the oesophageal atresia and/or tracheo-oesophageal fistula. *Congenital diaphragmatic hernia*: surgery to reduce the hernia and close the defect. *Intestinal atresia*: surgery, either temporising or definitive, to manage the obstruction including stoma formation and primary anastomosis. *Gastroschisis*: any procedure to either cover or reduce the bowel and/or close the defect. This includes application of a silo (regardless of whether or not they go on to require surgery). It excludes initial covering of the bowel in a plastic covering (bag or cling film) prior to intervention. *Exomphalos*: surgery or application of topical treatment to the sac in patients managed conservatively (regardless of whether or not they go on to require surgery). *Hirschsprung's disease*: surgery, either temporising or definitive, or rectal/distal bowel irrigation, laxatives or digital stimulation in patients managed conservatively. This does not include pre-operative washouts in patients planned to have surgery. *Anorectal malformation*: surgery, either temporising or definitive, or anal/fistula dilatation in patients with a low anorectal malformation managed conservatively.
American Society of Anesthesiologists Score at the time of primary intervention	1.Healthy person, 2. Mild systemic disease, 3. Severe systemic disease, 4. Severe systemic disease that is a constant threat to life, 5. A moribund patient who is not expected to survive without the operation, Not applicable — no intervention.
What type of anaesthesia was used for the primary intervention?	General anaesthesia with endotracheal tube, General anaesthesia with laryngeal airway, Ketamine anaesthesia, Spinal/caudal anaesthesia, Local anaesthesia only, No anaesthesia/just analgesia, No anaesthesia/no analgesia, Not applicable: no surgery or intervention undertaken.
Who undertook the anaesthetic for the primary intervention?	Anaesthetic doctor, Anaesthetic nurse, Medical officer, Surgeon, Other healthcare professional, No anaesthetic undertaken. If more than one of these personnel were present, please select the most senior.
Who undertook the primary intervention?	Paediatric surgeon (or junior with paediatric surgeon assisting/in the room), General surgeon (or junior with paediatric surgeon assisting/in the room), Junior doctor, medical officer or other (without a paediatric or general surgeon assisting/in the room), Trainee surgeon (without a paediatric or general surgeon assisting or in the room), Not applicable — no surgery or primary intervention undertaken.
Was a Surgical Safety Checklist used at the time of primary intervention?	Yes, No: but it was available, No: it was not available, Not applicable: a conservative primary intervention was undertaken, Not applicable: no surgery or primary intervention undertaken.
Total duration of antibiotics following primary intervention	In days (including the day of surgery and the day antibiotics were stopped. Include intravenous and oral antibiotics).
Did the patient receive a blood transfusion?	Yes: not cross-matched, Yes: cross-matched, No: not required, No: it was required but not available. Within 30 days of primary intervention or 30 days of presentation if no intervention was undertaken.
Did the patient require ventilation? If yes, for how long did the patient remain on ventilation?	Yes: and it was given, Yes: but it was not available, No. Within 30 days of primary intervention or 30 days of presentation if no intervention was undertaken. Please include all types of ventilation. In days (include all days on ventilation within 30 days of primary intervention or 30 days of presentation if no intervention was undertaken).
Time to first enteral feed (post-primary intervention)	In days (include the day of primary intervention and the day of first enteral feed in the calculation). Enter 0 if enteral feeds were not commenced. Enter 999 if feeds were not stopped, for example, in patients with Hirschsprung's Disease managed conservatively. Include all types of enteral feeding — oral, nasogastric, gastrostomy and other.
Time to full enteral feeds (post-primary intervention)	In days (enter 0 if the patient died before reaching full enteral feeds or 30 if the patient had not reached full enteral feeds at 30 days post-primary intervention or 30 days following admission in patients who did not receive a primary intervention). Include all types of enteral feeding — oral, nasogastric, gastrostomy and other.
Did the patient require parenteral nutrition? If yes, for how long did the patient receive parenteral nutrition?	Yes and it was given, Yes and it was sometimes available but less than required, Yes but it was not available, No. In days. Include all days that the patient received parenteral nutrition (any volume) up until 30 days post-primary intervention or 30 days following presentation in patients who do not receive an intervention.

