### Data quality

To ensure high quality of data, a detailed protocol for collaborators has been produced and published on the study website (www.globalpaedsurg.com) in 12 languages: English, French, Spanish, Portuguese, German, Italian, Chinese, Arabic, Korean, Lithuanian, Turkish and Russian. Clear and concise definitions have been provided for all data points on the protocol, on the data collection forms and within REDCap when entering the data. A study launch meeting was undertaken where the principal investigator presented the data collection process in detail, demonstrated use of REDCap and answered questions. This was recorded, circulated to all collaborators via email and placed on the website. A frequently asked questions document has been circulated via email and placed on the website. Two meetings were held by the principal investigator to detail the study, data collection process and answer questions among the country leads so they in turn can provide advice and support to local collaborators within their country. Again this was recorded, circulated and placed on the website.

A pilot study of the patient data collection form and institutional survey was undertaken by lead investigators to optimise the study design and to address any feasibility or other barriers to effective data collection and study completion across participating sites. The pilot study commenced on 1 August 2018 for 30 days in English, Spanish and French by 41 collaborator colleagues. The data collection forms were amended following feedback to clarify terminology, add important missing variables or descriptions and correct any translation errors. All translated data collection forms, REDCap and study documentation have been checked and verified by a native speaker for accuracy.

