### Data analysis

#### Patient and institutional data

Data will be analysed using Stata and SAS V.9.4 (Cary, North Carolina, USA). Missing data for the covariates will be analysed to determine whether it is related to the outcome and either complete-case analyses or multiple imputation techniques will be used for analyses accordingly.

Significant differences in mortality between LMICs and HICs will be determined for each of the study conditions using Χ^2^ analysis, or Fischer’s exact test if either group contains <10 patients. World Bank classification of low, middle and high income countries during the fiscal year 2018 will be used.^38^

Univariate logistic regression analyses will be conducted between covariates and the primary outcome of mortality. Based on the results, covariates with a p value <0.10 will be included in the multivariate model. The final multi-level multivariate logistic model will be determined using stepwise backward elimination to interventions and peri-operative factors affecting outcomes. Data will be adjusted for confounding factors and effect modifiers. Potential confounders include gestation age at birth, weight, time from birth to presentation and American Society of Anesthesiologists score at the time of primary intervention. Potential effect modifiers include administration of peri-operative antibiotics, fluid resuscitation, thermal control and provision of other condition-specific neonatal care such as parenteral nutrition in neonates with gastroschisis.

Multi-level multivariate logistic regression analysis will also be undertaken to identify institutional factors affecting mortality with adjustment for confounders. P<0.05 will be deemed significant.

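### In Table 1 the general-surgeon option for who undertook the primary intervention repeats the paediatric-surgeon bracket, so one type of supervised case fits two options and another fits none

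*Protocol article*

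**What the plan says.** In the protocol article, Table 1 (Clinical condition and patient care), the item on who undertook the primary intervention has five options. In printed order they are:

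1. "Paediatric surgeon (or junior with paediatric surgeon assisting/in the room"
2. "General surgeon (or junior with paediatric surgeon assisting/in the room"
3. "Junior doctor, medical officer or other (without a paediatric or general surgeon assisting/in the room"
4. "Trainee surgeon (without a paediatric or general surgeon assisting or in the room"
5. "Not applicable — no surgery or primary intervention undertaken"

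The item has no tie-break. The item directly above it, on who gave the anaesthetic, does have one: "If more than one of these personnel were present, please select the most senior".

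The Data quality section states: "Clear and concise definitions have been provided for all data points on the protocol, on the data collection forms and within REDCap". The Data analysis section, under Patient and institutional data, plans a mortality model in these terms: "The final multi-level multivariate logistic model will be determined using stepwise backward elimination to interventions and peri-operative factors affecting outcomes". Operator grade is not named there.

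**The concern.** The options should let a collaborator place each operated case in exactly one category. Because options 1 and 2 share a bracket, the supervision clause of option 2 points to the wrong specialty. One type of case then has two valid answers and another has none.

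Operator grade is a collected peri-operative item, and the second objective of the study is to find patient-level and hospital-level factors that could be modified to improve care. The item is therefore a natural candidate covariate for the factor analysis. If collaborators follow the text literally, some supervised cases will get an arbitrary code or none. Any contrast between paediatric surgeons, general surgeons and unsupervised juniors would then compare groups that are not cleanly defined.

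The planned validation may not reveal this. It re-collects a selection of data and measures agreement. If this item is among those re-collected and the same option text is used, two people can agree on the same wrong code.

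**Working it through.** The plan states no figure on this point, so the check is a case enumeration. Each combination of operator and supervisor is set against the five printed options, and then against the list with one word changed in option 2.

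| Case | Fits as printed | Fits if option 2 names a general surgeon |
|---|---|---|
| (a) Paediatric surgeon operates | 1 | 1 |
| (b) General surgeon operates | 2 | 2 |
| (c) Junior operates, paediatric surgeon present | 1 and 2 | 1 |
| (d) Junior or trainee operates, only a general surgeon present | none | 2 |
| (e) Junior doctor, medical officer or other, neither surgeon present | 3 | 3 |
| (f) Trainee surgeon, neither surgeon present | 4 | 4 |
| (g) No surgery or primary intervention | 5 | 5 |

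Reasoning for the two rows that fail:

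- **Row (c), overlap.** The brackets of options 1 and 2 are the same, so the case meets both. The item has no rule for choosing between them.
- **Row (d), gap.** The brackets of options 1 and 2 both require a paediatric surgeon, and none is present. Options 3 and 4 require that no general surgeon is present, and one is. Option 5 requires that nothing was done.

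The one-word change removes both failures and leaves the other five rows as they were. No other part of the article corrects or explains the bracket.

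The reach of the defect follows from where the item is used. The primary outcome is in-hospital mortality. It is compared between LMICs and HICs by chi-squared or exact test within each condition, and the Table 2 sample sizes rest on mortality by income group. None of these uses operator grade. Only the regression on interventions and peri-operative factors could.

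**The case against.** The strongest case on the other side is that this is a copying slip whose meaning is easy to recover. Options 3 and 4 exclude the presence of either kind of surgeon, which shows that supervision by a general surgeon was meant to belong to option 2. A collaborator in row (d) would most naturally choose option 2, and one in row (c) option 1, and both would then be coded as intended. Table 1 is also the article's rendering and not the live form. The Data quality section describes a pilot by 41 collaborators with amendments to clarify terminology, a circulated document of frequently asked questions, and native-speaker checks of the translations. Much of this stands. It limits the claim to what can happen under the printed text, because the article does not show that records were in fact misclassified. It does not remove the defect: the printed list still fails two of the seven cases, and nothing in the article shows that the bracket was right in REDCap.

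A reader might infer more: that the odds ratio for general versus paediatric surgeon is pulled towards 1 by a known amount, and more so in LMICs. The documents do not support this. Take mortality of 20% and 40%, both assumed, for a true odds ratio of (0.40/0.60)/(0.20/0.80) = 2.67. Then move a share of the paediatric group into the general group:

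- Equal groups, 20% moved: (0.40 + 0.2 × 0.20)/1.2 = 0.367, odds ratio 2.32.
- Equal groups, 40% moved: (0.40 + 0.4 × 0.20)/1.4 = 0.343, odds ratio 2.09.
- Equal groups, 30% junior-led and 20% of those miscoded, so 0.3 × 0.2 = 6% moved: (0.40 + 0.06 × 0.20)/1.06 = 0.389, odds ratio 2.54.
- General group four times the paediatric group, 20% moved: (4 × 0.40 + 0.2 × 0.20)/4.2 = 0.390, odds ratio 2.56.

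Every input is assumed, and the result runs from 2.09 to 2.56 according to the choice. The last line also goes against the LMIC inference: where general surgeons do most of the work, the same share of miscoding does less harm in this model. The model covers only the overlap. Cases in the gap may be entered under options 1 to 4 or left blank, and the direction of bias then depends on where they go and on their own mortality.

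**Conclusion.** The response list is wrong as printed. It has one overlap and one gap, both caused by a single word in the bracket of option 2, and this conflicts with the article's statement about its definitions. Operator grade can be misclassified or left blank for juniors under supervision. A surgeon of either kind who operates personally is coded correctly, and so are unsupervised juniors and trainees.

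The size and direction of any resulting bias cannot be computed, because the article gives no frequency of supervised junior-led procedures and no mortality by operator. The consequence is confined to a possible covariate in the peri-operative factor analysis. The LMIC versus HIC mortality comparison and the sample sizes are unaffected.

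The practical effect rests on two things that the article does not show: whether the live form carried the printed text, and whether collaborators followed it literally. The point is a small correction worth making and does not threaten the main result.

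**What to change.** Change the bracket of the general-surgeon option so that it refers to a junior with a general surgeon assisting or in the room. Check Table 1 against the REDCap form, the paper forms and all 12 language versions (English included).

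If only the article carries the slip, correcting Table 1 is enough. If the live form carried it, correcting the form does not repair records already entered: recruitment ran from October 2018 to April 2019, and primary data collection was due to end on 29 June 2019. In that case, where sites can still trace the cases, ask them to check junior-led records under options 1 to 4 and any blanks. A check of general-surgeon records alone would miss gap cases entered elsewhere.

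Where tracing is no longer possible, and it may not be since the REDCap data are anonymous, either run a sensitivity analysis that merges the paediatric-surgeon and general-surgeon categories or report the ambiguity as a limitation. Merging settles the overlap and any gap case entered under either surgeon. It does not recover gap cases entered as junior or trainee or left blank, and it gives up the contrast between the two specialties.

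The cost is one word in the form and its language versions, and a small amount of site checking.

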**Outcomes**	
Did the patient survive to discharge? If the patient was discharged prior, were they still alive at 30 days following primary intervention? If no, cause of death?	Yes, No. Select yes if the patient was still alive in your hospital 30 days after primary intervention or 30 days after presentation in patients who did not receive a primary intervention. Yes, No: not followed-up after discharge, Followed-up but not until 30 days post-primary intervention. This can include all reliable communication with the patient/patient’s family including in person, via telephone and other. Sepsis, aspiration pneumonia, respiratory failure, cardiac failure, malnutrition, electrolyte disturbance, haemorrhage, lack of intravenous access, hypoglycaemia, recurrent tracheo-oesophageal fistula, recurrent diaphragmatic hernia, anastomotic leak, ischaemic bowel, ruptured exomphalos sac, enterocolitis, other. If other, please specify.
Duration of hospital stay (days)	Please include the day of admission and the day of discharge in your calculation. For example, if a patient presented on 1 October and was discharged on the 5 October, their duration of hospital stay would be 5 days. If the patient died, please record the number of days from admission to death. Only include the duration of the primary admission, not subsequent admissions if the patient re-presented.
Did the patient have a surgical site infection?	Yes, No, Not applicable: no surgical wound. This is defined as one or more of the following within 30 days of surgery: (1) purulent drainage from the superficial or deep (fascia or muscle) incision, but not within the organ/space component of the surgical site OR (2) at least two of: pain or tenderness, localised swelling, redness, heat, fever, AND the incision is opened deliberately to manage infection, spontaneously dehisces or the clinician diagnoses an SSI (negative culture swab excludes this criterion) OR (3) there is an abscess within the wound (clinically or radiologically detected).
Did the patient have a full thickness wound dehiscence?	Yes, No, Not applicable — no surgical wound. This is defined as all layers of the wound opening within 30 days of surgery.
Did the patient require a further unplanned intervention?	Yes — percutaneous intervention, Yes — surgical intervention, No, Not applicable — no primary intervention undertaken. Within 30 days of primary intervention. This does not include routine reduction and closure of the defect in neonates with gastroschisis receiving a preformed silo.
Was the patient followed up at 30 days post primary surgery or intervention to assess for complications?	Yes: reviewed in person, Yes: via telephone consultation, Yes: via other means, Yes: still an in-patient at 30 days, No: data are based on in-patient observations only, No: follow-up was done but prior to 30 days.
If the patient had a complication, when was it diagnosed?	During the primary admission, As an emergency re-attender, At routine follow-up as an outpatient, Not applicable: no complications.
What study condition does this patient have?	Oesophageal atresia, Congenital diaphragmatic hernia, Intestinal atresia, Gastroschisis, Exomphalos/Omphalocele, Anorectal malformation, Hirschsprung's Disease. If the patient has presented for the first time with more than one of these conditions, please select all that apply. If the patient presented on this occasion with one of these conditions, but previously had another condition managed then only select the condition they are presenting with on this occasion and enter that they have another anomaly in the demographics section above. For example, if the patient presents at 2 months with Hirschsprung's disease, but previously had a duodenal atresia repair, please select Hirschsprung's disease here (not intestinal atresia) and tick in the section above that they have another gastrointestinal anomaly.

SIRS, Systemic Inflammatory Response Syndrome.

The secondary outcomes include complications occurring within 30 days of primary intervention:

Surgical-site infection.Wound dehiscence.Need for re-intervention.Condition-specific complications.Condition specific outcome variables.Length of hospital stay or time from admission to death in patients who do not survive.30-day post-primary intervention mortality.

Secondary outcomes will not be collected on patients who do not receive a primary intervention within 30 days of hospital admission, with the exception of length of hospital stay or time from admission to death. Thirty-day follow-up will be undertaken within the capacity of the collaborating team; no additional funding will be provided.

